### Premature termination

#### Withdrawal of individual subjects

Subjects can end participation in the study at any time without providing a reason and without consequences for their future treatment in the clinic. The investigator can decide to withdraw a subject from the study for urgent medical reasons. Subjects withdrawn from the study will continue their regular follow-up outside of the study protocol. Subjects will be replaced if they withdraw before pump implantation has taken place. Subjects who withdraw after pump implantation has taken place will not be replaced. With subject agreement, a final assessment will take place before definite ending of participation. These subjects will not be included in the analysis but we will present a fact sheet including their information.

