For each assessment, one assessor will make a standardized video recording during trials for each of the three functional ability goals. The recording procedure will be identical for all measurements. Another assessor, blinded for group allocation, will rate the subject’s performance from the video recordings. Although the GAS only simulates the subject’s own functional setting, parents were convinced that the outcome of scaling was representative of their own setting
[19].

Goal attainment scores will be recorded at baseline, after three months of blinded treatment and after nine months of ITB treatment. Goal attainment change scores will be determined by subtracting the baseline score from the outcome score. Subjects who achieve a GAS T-score >50 achieved their goals
[8]. Clinical relevance will be defined as an improvement of at least two points in at least one of the three goals
[19].

A single aggregated score (T-score) can be produced by a standardized mathematical formula: Overall GAS = 50+ 10∑(w_i_x_i_) / √((1-ρ) ∑w_i_^2^ + ρ(∑w_i_)^2^); W_i_ is the weight assigned to the goal, x_i_ is the numerical value achieved (between -3 and +2), ρ (rho) is the expected correlation of the goal scales, which is normally 0.3
[13,14].

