#### Other study parameters

To assess the safety of ITB treatment, side effects and complications will be closely monitored. The complication rate will be calculated by dividing the number of complications by the duration in years of pump implantation.

Functional abilities at baseline will be assessed by the Paediatric Evaluation of Disability Inventory (PEDI) and will be repeated after three and twelve months. The PEDI was developed for children from six months to seven and a half years of age and assesses skills in mobility, self-care and social function. It can also be used for older children if their functional abilities are expected to be below the level of a child of seven and a half years old. The functional scales indicate if children with disability are able or unable to perform certain activities. Separate measures assess the degree of caregiving assistance and equipment modification that is needed to accomplish complex functional skills. Scores on the caregiver assistance scale are noted on a range from independent to maximal assistance and modification scores are scored as none, child-oriented, rehabilitation-oriented or extensive
[37,38]. The PEDI will be administered through direct assessment by a therapist.

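### A subject the investigator withdraws before month 3 leaves both study follow-up and the analysis, and the plan gives no route to stay in for the month-3 GAS or complication recording

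*Protocol article*

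**What the plan says.** All the rules come from the protocol article. Under *Withdrawal of individual subjects*:

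- The investigator's power is over participation in the study as a whole: "The investigator can decide to withdraw a subject from the study for urgent medical reasons".
- What follows is ordinary care: "Subjects withdrawn from the study will continue their regular follow-up outside of the study protocol".
- One more study contact is foreseen, and it is conditional: "With subject agreement, a final assessment will take place before definite ending of participation".
- "Subjects who withdraw after pump implantation has taken place will not be replaced".
- "These subjects will not be included in the analysis but we will present a fact sheet including their information".

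Under *Primary outcome measure*, the schedule is: "Goal attainment scores will be recorded at baseline, after three months of blinded treatment and after nine months of ITB treatment". Under *Other study parameters*, safety is summarised as a rate: "The complication rate will be calculated by dividing the number of complications by the duration in years of pump implantation". That section does not say whether a withdrawn subject's later events or later pump time count.

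**The concern.** Two separate events are handled by one rule. One is a medical decision about a subject's treatment. The other is the end of observation. Once the investigator withdraws a subject, both have happened, and the text describes no status in which the subject is off study treatment but still observed by the study.

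For efficacy, a subject withdrawn in, say, week 5 has at most a week-5 assessment. The month-3 score on which the arms are compared is not planned for that subject, and the subject is excluded in any case. Repairing only one of these is not enough. Lifting the exclusion does not create a month-3 value, and collecting the value is of no use while the exclusion stands.

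The loss is unlikely to be random. During the blinded three months, overdose of the infused drug or its withdrawal can arise only in the ITB arm, and the *Dosage* section itself foresees withdrawal signs in that period. Deterioration can also prompt an exit. Either way, those who remain are a selected group.

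For safety, the Objectives ask what the side effects of ITB are. A withdrawn subject may still carry the pump, yet complications after exit arise where the study plans no recording.

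**Working it through.** **Inputs** (*Sample size calculation*): anticipated change 0 (SD 8.5) on placebo and 12.5 (SD 10) on ITB; two-sided 5% t-test; 90% power; 13 per group needed, 15 enrolled.

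**Step 1: the plan's own figure.** Pooled SD = √((8.5² + 10²)/2) = 9.28. With the noncentral t distribution, 12 per group gives 88.3% power and 13 per group gives 90.9%. The stated 13 is reproduced. With 15 per group, power is 94.5%.

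**Step 2: bias from excluding the lost subjects.** Assume k of 15 ITB subjects are withdrawn before month 3 and would have shown change c at month 3, while the others average 12.5. The mean with full follow-up is ((15 − k) × 12.5 + k × c)/15. The analysed mean is 12.5. Both k and c are assumptions.

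Two values of c are shown. The first is no change, c = 0. The second is the lowest the scale allows: all three goals fall from −2 to −3. With unit weights and ρ = 0.3, one goal point is worth 10/√(0.7 × 3 + 0.3 × 9) = 10/√4.8 = 4.56 T-score points, so c = −3 × 4.56 = −13.7.

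| k | Full mean, c = 0 | Overstated by | Full mean, c = −13.7 | Overstated by |
|---|---|---|---|---|
| 1 | 11.7 | 0.8 | 10.7 | 1.7 |
| 2 | 10.8 | 1.7 | 9.0 | 3.5 |
| 3 | 10.0 | 2.5 | 7.3 | 5.2 |

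Example, k = 2 and c = 0: 12.5 × 13/15 = 10.8, and 12.5 − 10.8 = 1.7.

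**Step 3: power does not reveal the problem.** With the lost subjects excluded (15 against 14, 13 or 12), power is 93.7%, 92.8% and 91.6%. The two extra subjects per group protect the sample size but not the comparison. With all 15 per group observed and included, and c = 0, power is about 90%, 84% and 76%.

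**Step 4: direction.** Bias against ITB is also possible. If one placebo subject who would have fallen by 13.7 is excluded and the other 14 average 0, the placebo mean is 0 instead of −13.7/15 = −0.9, and the ITB effect is understated by 0.9 points.

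**The case against.** Several points against the concern carry weight.

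- **Withdrawal is discretionary.** A reader might infer that every subject whose treatment is stopped must leave the study. The text does not say so. The *Dosage* section allows action on suspected pump or catheter problems when the subject's condition demands it, and the randomization section allows emergency code-breaking. Neither mentions leaving. The concern covers only subjects the investigator does withdraw.
- **Not everything is lost.** A reader might also infer that these subjects' month-3 scores and complications never reach the record. That is too strong. A subject who leaves after month 3 already has the primary score. A fact sheet on withdrawn subjects is promised, side effects are to be closely monitored, and the data safety monitoring board reviews individual safety data. Events up to exit are plausibly recorded. What remains is that no month-3 score and no complication recording are planned after exit.
- **The counts are assumed.** If pump removal were the only reason for exit, the numbers would be small. The article's 1.2 removals do not follow from its 5.9%: 5.9% of 3.5 infections is 0.2, and 5.9% of 30 patients is 1.8. Half of these in the ITB arm is 0.1 to 0.9 subjects, or 12.5 × 0.1/15 = 0.1 to 12.5 × 0.9/15 = 0.75 points with c = 0. This stands as a caution about size. Removal is, however, not the only urgent medical reason.
- **No safety figure can be given.** It is tempting to compute how far the infection rate would fall if subjects with removed pumps dropped out of it. That means deleting events that happened before exit, which the text does not clearly prescribe, and it needs the removal count just shown to be unreliable. After removal, moreover, no further implanted time accrues.
- **The article condenses a fuller protocol.** Post-exit safety procedures may well be set out there, so the point on later complications is the weaker half. The rules on withdrawal, follow-up and exclusion are stated outright, and a fuller document would have to reverse them to remove the difficulty.

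**Conclusion.** The concern holds in a limited form. A subject whom the investigator withdraws on urgent medical grounds before month 3 has no planned month-3 GAS, no planned study recording of later complications, and no place in the analysis. The only remaining contact is an exit assessment that depends on agreement. The text offers no way to stay under study observation.

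The resulting bias cannot be estimated from the article. If 1 to 3 of 15 ITB subjects are lost and would have shown no change, the effect is overstated by 0.8 to 2.5 points on an anticipated 12.5. If they had deteriorated to the bottom of the scale, the figure reaches 5.2. Exits on placebo could move it the other way. With 30 subjects and a stated aim of level-one evidence, a few selective losses matter, and the change should be made. The documents do not support saying that stopping treatment always means leaving, that the data are wholly lost, or that the complication rate falls by any given amount.

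**What to change.** In *Withdrawal of individual subjects*:

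1. Distinguish discontinuing study treatment from withdrawing consent to follow-up. The medical decision itself is left as it is.
2. State that, unless consent to follow-up is withdrawn, the subject stays in the study for the scheduled month-3 GAS, the month-12 visit and complication recording.
3. Replace the exclusion rule with analysis in the randomised group, using whatever has been collected. The fact sheet can stay as a supplement.
4. Keep the exit assessment for those who refuse further visits.

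In *Other study parameters*, state that these subjects' complications and implanted pump time count in the rate.

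The cost is a short amendment plus visits already on the schedule, for a few subjects who remain in regular clinic follow-up anyway. Those families carry some visit burden. The observed ITB effect may be smaller, and power lower than the completers-only figure suggests.

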## Methods/Design

### Study design

The design of the study is a double blind placebo-controlled multi-center randomized clinical trial. It will be conducted in the VU University Medical Center (VUMC) in Amsterdam and the Maastricht University Medical Center (MUMC) in Maastricht (both in the Netherlands). The Medical Ethical Committee of the VU University Medical Center approved the study. In both centers local practicability was granted subsequently. Subjects will be included over a period of two and a half years and they will participate in the study for one year. Figure 
1 shows the flow scheme for subjects and timing of measurements throughout the study.

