### Intervention

Included subjects will be randomized in two groups. Group 1 will receive placebo treatment via an implanted micro-infusion pump for three months. Group 2 will receive ITB treatment via an implanted micro-infusion pump for three months. In our opinion, it is unethical to continue placebo treatment for more than three months. If interim analysis shows that subjects in one of the groups have significant disadvantages compared to the other group, the study will be prematurely terminated. On the other hand, we know from experience that dosages for some patients are still being modified three months after starting treatment. As a consequence, the effect of treatment in these patients may not yet be optimal, which may then result in no detectable effect of ITB treatment at that point. We will try to reduce this possible effect through frequent dose modification. Patients will be seen once or twice weekly to increase their dosage, until either a stable dosage or a maximal dosage of 800 μg/day is achieved.

Subjects will be assessed at three months and the effect of treatment in the two groups compared. Since determining the most beneficial pump setting can take more than three months and because the initial effect may recede in some cases, all subjects will receive subsequent ITB treatment for nine months. Following this 9 month period, clinical evaluation will be performed in order to determine long-term effects (see Figure 
1. Flow Chart of Subjects).

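### The rule excluding every post-implantation withdrawal, as written even one with a recorded 3-month GAS score, leaves the randomised comparison open to bias of unknown size and direction

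*Protocol article*

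**What the plan says.** The rule is in the protocol article under Withdrawal of individual subjects.

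- Patients may leave whenever they wish: "Subjects can end participation in the study at any time without providing a reason".
- The investigator may also remove them: "The investigator can decide to withdraw a subject from the study for urgent medical reasons".
- Before implantation a withdrawn patient is replaced. Afterwards: "Subjects who withdraw after pump implantation has taken place will not be replaced".
- An exit visit is offered: "With subject agreement, a final assessment will take place before definite ending of participation".
- The section then closes with the exclusion: "These subjects will not be included in the analysis but we will present a fact sheet including their information".

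The timing comes from other sections. Under Intervention: "Subjects will be assessed at three months and the effect of treatment in the two groups compared". Under Primary outcome measure: "Goal attainment scores will be recorded at baseline, after three months of blinded treatment and after nine months of ITB treatment". Under Study design, of the subjects: "they will participate in the study for one year".

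The Statistics section names the tests (independent samples t-test, or Mann–Whitney if normality fails) but no analysis set. Nothing elsewhere in the article overrides the exclusion.

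**The concern.** Randomisation makes the arms comparable only if the patients analysed are those randomised, or if the losses have nothing to do with arm and outcome. This rule breaks that link in two ways.

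First, a patient who leaves before three months is dropped, with no missing-data method in place of the score. Such a departure may reflect how the patient was doing, and the route for urgent medical reasons makes that plausible.

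Second, a patient who leaves in months 3 to 12 already has the blinded primary score. By then the former placebo group has just started ITB while the other group continues it, so the reasons for leaving can differ by arm. Events in the open-label phase would then decide which blinded scores count.

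At stake is the primary estimate of a trial of 30 patients, where one or two patients per arm can move a mean visibly.

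**Working it through.** **Inputs.** From Sample size calculation: placebo change 0 (SD 8.5), ITB change 12.5 (SD 10), two-sided 5%, 90% power, 13 per group needed, 15 per group enrolled. The article gives no withdrawal rate, no split by arm and no outcomes of withdrawn patients. Every withdrawal scenario below is therefore an assumption.

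**The plan's own figure.** Pooled SD = √((8.5² + 10²)/2) = 9.28. Noncentrality = 12.5 / (9.28 × √(2/n)).

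- n = 12: 3.30, power 88.3%
- n = 13: 3.43, power 90.9%
- n = 15: 3.69, power 94.5%

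Thirteen is the smallest n that reaches 90%, so the stated figure reproduces.

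**Selective loss, no true effect.** Both arms have mean change 0, SDs 10 (ITB) and 8.5 (placebo), and 15 per arm. The lowest k values are removed and a Student t-test is applied to simulated trials.

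- Worst 1 or 2 ITB patients only: bias +1.2 or +2.3 T-points. Two-sided type I error is about 7.6% or 12.2% instead of 5%. This is a worst case.
- Worst 1 or 2 placebo patients only: bias about -1.1 or -2.0 points, against ITB.
- Worst 1 or 2 from each arm: bias +0.2 or +0.3 points. Type I error is about 7.0% or 8.5%, because trimming both arms shrinks the observed spread.
- Loss unrelated to arm and outcome: bias 0 and type I error 5%. Losing 2 per arm takes power from 94.5% to 90.9%.

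*Hand check of the bias.* The expected lowest of 15 standard normal values is -1.736 and the second lowest -1.248. Removing one raises the mean of the rest by 1.736/14 = 0.124 SD. Removing two raises it by (1.736 + 1.248)/13 = 0.230 SD. For ITB that is 10 × 0.124 = 1.2 and 10 × 0.230 = 2.3. For placebo it is 8.5 × 0.124 = 1.05 and 8.5 × 0.230 = 1.95.

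**Selective loss at the planned effect.** Suppose all 15 ITB patients average 12.5 and those who leave had no gain. With one excluded, the analysed mean is (15 × 12.5 − 0)/14 = 13.4. With two excluded it is 187.5/13 = 14.4. The overstatement is 0.9 or 1.9 points.

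**The case against.** A reader might infer that the comparison is biased, and in favour of ITB. The article does not support that.

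- Patients may leave without giving a reason, so it cannot be said that withdrawal follows lack of effect or side effects.
- Both arms carry an implanted pump, so the 3.5 infections and 1.2 removals expected among 30 patients threaten both.
- Placebo patients without benefit may also leave, which would push the estimate against ITB.
- Blinding, and the promise of ITB for everyone after three months, weaken the motive to leave early.

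All of this stands. It removes any claim about direction and makes the one-arm figures a worst case. It does not make the rule safe.

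A reader might also infer that the trial becomes underpowered. It does not: enrolling 15 instead of 13 per group covers the loss of two per arm. That allowance protects power, however, and not the comparability of the arms.

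Nor are the withdrawn patients' data thrown away, since the fact sheet reports them. They are only kept out of the comparison.

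Finally, the article never discusses a patient who leaves after three months, so the loss of that patient's score is a literal reading of a sentence without a time limit. The authors may not have intended it. If the words for the excluded subjects refer only to those who had an exit visit, the rule still excludes withdrawn patients who have data. A fuller analysis plan may exist, but this is a rule the article states, not a detail it leaves out.

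**Conclusion.** The point holds as a risk created by a stated rule. As written, every randomised and implanted patient who withdraws during the year leaves the analysis, including one with a recorded blinded 3-month score. The comparison is open to bias, but bias has not been shown.

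In the scenarios with no true effect and one or two losses per affected arm, the shift runs from about -2.0 to +2.3 T-points, and is zero if withdrawal is unrelated to arm and outcome. Against a planned difference of 12.5 points that is modest. Against a nominal 5% error rate it is not negligible: about 12.2% in the worst ITB-only case with two patients removed. These sizes rest on assumed numbers and patterns of withdrawal, normal scores and the planning SDs.

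The rule should be changed, because the error it can cause is avoidable and the data to avoid much of it are already being collected. It does not undermine the design or the sample size.

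**What to change.** Replace the exclusion sentence with: *All randomised patients who undergo implantation are analysed in their allocated group; any recorded 3-month GAS score is used whatever happens later.*

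For patients who leave before three months, pre-specify one missing-data method and sensitivity analyses around it. Candidates are the exit assessment already planned, a no-change score of -2 per goal, and a pessimistic -3 per goal. None is clearly right as the primary value. An exit assessment falls off schedule, possibly during titration; a fixed -2 understates variance; and -3 records a deterioration nobody observed. With three goals, unit weights and ρ = 0.3, the T-score divisor is √(0.7 × 3 + 0.3 × 9) = 2.19. Moving from -2 to -3 on all goals therefore costs 10 × 3/2.19 = 13.7 T-points, a demanding test.

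Keep the fact sheet. The present exclusion can remain, at most, as a per-protocol sensitivity analysis.

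The cost is one paragraph of wording, with no new visits or patients and no change in sample size. The ITB estimate may become slightly less favourable.

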#### Data safety monitoring board

A data safety monitoring board will be formed and will meet periodically to review aggregate and individual subject data related to safety, data integrity and overall conduct of the trial. They will assess the risk/benefit balance, including a statistical analysis if necessary. Depending upon this assessment, the board will provide recommendations to continue, adapt or terminate the trial.

### Statistics

#### Descriptive statistics

Patient characteristics will be described. Gender distribution will be compared between the ITB and placebo group using a Chi-square test. Mean age between the ITB and placebo group will be compared using an independent samples t-test. Means and standard deviation (SD) of the PEDI scores, C-BiLLT scores, GAS t-score, BAD score, SPAT score and mean EMG activity at baseline will be tabulated. Means and SD of the GAS t-score, BAD score, DIS score, SPAT score and mean EMG activity at follow up will be separately tabulated per group.

#### Univariate analysis

The GAS t-scores, BAD score, SPAT score and EMG activity in the placebo and ITB group will be compared using an independent samples t-test. If the assumption of normality appears not to be valid, the non-parametric Mann–Whitney test will instead be used. A p-value of 0.05 is considered statistically significant for this primary analysis. To assess within-group changes in means between follow-up times and baseline GAS t-scores, BAD score, DIS score, SPAT score and EMG activity, a paired t-test or non-parametric Wilcoxon test will be used (depending on whether the normality assumption is valid). In these analyses, a p-value of 0.05 is considered to be statistically significant.

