### Secondary outcome measures

#### Dystonia

Videos of all patients will be made using the video protocol described by Monbaliu et al.
[20]. Blinded therapists or physicians will assess all videotapes and rate dystonia using the Barry-Albright dystonia (BAD) scale and the Dyskinesia Impairment Scale (DIS).

The BAD scale is a five point ordinal severity scale to assess secondary dystonia in eight body regions (eyes, mouth, neck, trunk, each upper and lower extremity)
[21]. Raters score dystonia as none, slight, mild, moderate or severe. A reduction of 25% or more, in comparison with the baseline score, is considered clinically significant. In our experience, interrater variability is high, but BAD scores are generally accepted as a measurement of dystonia and are widely used to assess dystonia.

Recently, a new instrument to measure dystonia in dyskinetic CP became available, the DIS
[20]. It consists of two subscales: dystonia and choreoathetosis. Scoring is carried out in 12 body regions all in two conditions (rest and activity). Both duration and amplitude are evaluated. Since this is a new instrument, we will use the DIS in addition to the BAD.

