#### Electromyography

The DIS has no external validation. We decided that Surface Electromyography (EMG) might provide an impression of muscle activity level underlying dystonia. Therefore, surface EMG measurements will be carried out to determine mean EMG activity in individually determined muscle groups and in multiple conditions such as rest and during activities.

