#### Spasticity

The soleus Hoffmann-reflex (H-reflex) represents excitability of the neural components of the stretch reflex arc
[22]. The H/M-ratio of the H-reflex represents an increased excitability of soleus motor neurons. The H/M-ratio is increased in subjects with spasticity due to various origins,
[23] and it has been shown that the H_max_ decreases significantly after ITB administration in children with spastic cerebral palsy when compared with baseline measurements. This represents a decrease in motor neuron excitability. Furthermore, the response appears to be dose-dependent
[22]. Although not all children tolerate the measurements, feasibility of the H-reflex was 93% in a study by Hoving and co-workers
[22].

For clinical assessment of spasticity in children with central motor disorders, the spasticity test (SPAT) is used during standard physical examination. When using the SPAT, we will follow a standardized protocol as described in the guideline for standard physical examination of children with central motor disorders
[24,25]. The difference between the range of motion and the angle of catch will be used as the outcome measure for spasticity
[26]. The test takes approximately 5 to 8 minutes per limb to perform
[25]. This test might be difficult to perform in children and adolescents with severe dystonia and its usefulness will become evident during the study.

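### The between-group tests of BAD, SPAT and EMG carry no baseline term, which costs precision on secondary outcomes, and EMG levels from individually chosen muscles are pooled across patients

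*Protocol article*

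**What the plan says.** In the protocol article, the Univariate analysis section fixes the between-group test: "The GAS t-scores, BAD score, SPAT score and EMG activity in the placebo and ITB group will be compared using an independent samples t-test". Mann–Whitney replaces it if normality fails. Neither test is given a baseline term, and the sentence does not say whether follow-up values or changes are compared.

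Baseline values exist. The Descriptive statistics section says "GAS t-score, BAD score, SPAT score and mean EMG activity at baseline will be tabulated". In the Univariate analysis section they enter only paired tests within each arm, with Wilcoxon as the non-parametric alternative; the sentence begins "To assess within-group changes in means between follow-up times and baseline GAS t-scores, BAD score, DIS score, SPAT score and EMG activity, a paired".

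Three other sections bear on the point:

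- Dystonia, on the BAD scale: "A reduction of 25% or more, in comparison with the baseline score, is considered clinically significant".
- Spasticity, on SPAT: "The difference between the range of motion and the angle of catch will be used as the outcome measure for spasticity".
- Electromyography: the quantity is "mean EMG activity in individually determined muscle groups and in multiple conditions such as rest and during activities". No normalisation and no common set of muscles is stated.

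The Multivariate analysis section covers functional outcome and dystonia, with GMFCS, MACS, MRI class and co-medication. It lists no baseline outcome score and does not mention SPAT or EMG.

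**The concern.** BAD and SPAT carry the randomised answers to the first two secondary questions in the Objectives: whether ITB reduces dystonia and whether it reduces spasticity. The trial has 15 patients per arm, a number set for GAS alone. A between-group test without baseline leaves the stable differences between patients in the error term, although the data to remove them are already collected. It also takes no account of the clinical criterion for BAD, which is defined against the patient's own starting score.

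For EMG the question is also what is being compared. If the muscles differ from patient to patient, a group mean of follow-up amplitude averages different muscles, and differences between muscles and recording sites become part of the between-patient spread against which the treatment effect is judged.

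**Working it through.** **The plan's own figure.** The only sample size stated is for GAS: change 0 (SD 8.5) against 12.5 (SD 10), two-sided 5%, 90% power, 13 per group. The pooled SD is √((8.5² + 10²)/2) = 9.28. The noncentral t gives 88.3% power at 12 per group and 90.9% at 13, so 13 is reproduced. At 15 per group it is 94.5%. No such figure is given for BAD, SPAT or EMG.

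**Why GAS is unaffected.** Every goal starts at −2. With three goals, unit weights and ρ = 0.3, baseline T = 50 + 10 × (−6)/√(0.7 × 3 + 0.3 × 9) = 50 − 60/√4.8 = 22.6 for every patient. A constant cannot act as a covariate, and subtracting it changes nothing.

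**Precision for BAD and SPAT.** Let r be the correlation of baseline with 3-month value, with equal variances. The article gives no r, so the range is an assumption. Relative to a t-test on follow-up values (variance 1):

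- change score: 2(1 − r)
- ANCOVA: 1 − r²
- ANCOVA relative to change score: (1 − r²)/(2(1 − r)) = (1 + r)/2

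Power is shown for 15 per group and an assumed effect of 0.8 SD. The follow-up t-test then has 56%.

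| r | ANCOVA / follow-up variance | change / follow-up variance | ANCOVA / change variance | power, change | power, ANCOVA |
|---|---|---|---|---|---|
| 0.3 | 0.91 | 1.40 | 0.65 | 43% | 60% |
| 0.5 | 0.75 | 1.00 | 0.75 | 56% | 68% |
| 0.7 | 0.51 | 0.60 | 0.85 | 78% | 84% |
| 0.8 | 0.36 | 0.40 | 0.90 | 92% | 94% |

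These ratios ignore the cost of estimating the slope. With 15 per group that inflates the ANCOVA variance on average by about 1 + 1/(2 × 15 − 4) = 1.04, so at r = 0.3 the ratio is nearer 0.91 × 1.04 = 0.95 and the 60% is slightly optimistic.

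**Chance imbalance.** The standard error of the baseline difference is √(2/15) = 0.365 SD, so an imbalance above 0.5 SD has probability of about 17%.

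**EMG illustration.** All inputs are assumed: a true 25% reduction, within-patient log SD of 0.2, and 15 per group. The between-patient log SD, which stands for muscle and electrode differences, is varied. Power by simulation:

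| between-patient log SD | t-test on follow-up level | t-test on log(follow-up/baseline) |
|---|---|---|
| 0 | 96% | 77% |
| 0.3 | 53% | 76% |
| 0.6 | 19% | 77% |
| 1.0 | 8% | 77% |

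The ratio is insensitive to the spread between muscles; the level is not. With no such spread the ratio is the weaker analysis, which is a reason to consider log follow-up adjusted for log baseline.

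**The case against.** A reader might infer that the plan has decided to discard baseline. The text does not establish that. The Sample size calculation section plans the same t-test on GAS change, one sentence in the Univariate analysis section covers all four measures, and the BAD criterion is relative to baseline, so a change-score reading is possible. Against it, change scores are defined for GAS only, and the Univariate analysis section uses the word changes only for the within-group tests. The wording is open. If changes were meant, the gain from ANCOVA is smaller at high r, and subtraction already removes much of the different-muscles problem in EMG.

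A reader might also infer that chance imbalance biases the result. It does not. Under randomisation the unadjusted test is valid and its standard error already allows for imbalance.

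Showing only high correlations would overstate the gain. At r = 0.7 the trial behaves like 30/0.51 = 59 patients, but at r = 0.3 only like 30/0.91 = 33. The article itself reports high interrater variability for BAD and expects SPAT to be difficult in severe dystonia, and both would pull r down.

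For EMG, it would go beyond the text to say that the amplitudes are raw or that muscle choice dominates the variance. The article is silent on normalisation, which a full protocol may specify, and gives no variance figure. Muscles chosen before treatment add noise, not bias. EMG is also given only a supporting role.

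Finally, covariates are often left to an analysis plan, and the multivariate model for dystonia might include baseline. That does not help SPAT or EMG, which it does not mention. And the article does more than stay silent: it names a between-group test without a baseline term.

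**Conclusion.** The point holds as a loss of precision on secondary outcomes. The primary GAS analysis and its sample size stand.

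For BAD and SPAT the size depends on an r that the article does not give: a small gain at 0.3, roughly half the variance removed at 0.7. If change scores were intended, ANCOVA still has the lower variance across the range shown, with the advantage narrowing from 35% at r = 0.3 to 10% at r = 0.8. Below r = 0.5 a change score is less precise than follow-up alone, so ANCOVA is preferable under either reading.

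For EMG, as written, follow-up levels from individually determined muscle groups would be pooled into one group mean and tested. Such a comparison mixes different muscles and is hard to interpret. How much power it loses cannot be known from the article; the illustration shows only that the loss could be large or nil, depending on the spread between muscles.

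Adding centre as a factor is not part of this point, because the article does not settle whether the two pharmacies hold separate randomisation lists.

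**What to change.** - **BAD and SPAT** (and DIS, if it is compared between groups): analyse the 3-month value by ANCOVA on treatment and the patient's own baseline, and report the adjusted difference with its 95% CI.
- **EMG:** analyse log(follow-up/baseline) for the same muscles and the same condition within each patient, or log follow-up adjusted for log baseline. State any normalisation used.
- **Wording:** say in the Univariate analysis section which quantity is compared, so that follow-up and change can no longer both be read into it.

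The cost is about one degree of freedom per model (27 instead of 28 with 15 per group). No new data or visits are needed, and the primary analysis does not change.
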